**E. PROTECTION OF HUMAN SUBJECTS________________________________________________________**

1. RISKS TO THE SUBJECTS

*a. Human Subjects Involvement and Characteristics*

*- Describe the proposed involvement of human subjects.*

*- Describe the characteristics of the subject population, including their anticipated number, age range and health status.*

The proposed involvement of human subjects is limited to the exposure of Mozart music to a subset of subjects while they are asleep. Everything else pertaining to the daily routine of each subject will remain unchanged. The subject population all have disabilities and special needs and are permanent residents of the Thad E. Saleeby Center. The age range is large (approximately 5 to 90 years old). Many of the individuals have epilepsy or a seizure disorder and would possibly benefit from this study.

**Targeted/Planned Enrollment Table**

Total Planned Enrollment Will contact [name] and [name] for these numbers…

| TARGETED/PLANNED ENROLLMENT: Number of Subjects | | | |
| --- | --- | --- | --- |
| **Ethnic Category** | Sex/Gender | | |
| Females | Males | Total |
| Hispanic or Latino |  |  |  |
| Not Hispanic or Latino |  |  |  |
| **Ethnic Category: Total of All Subjects*** |  | | |
| **Racial Categories** |  | | |
| American Indian/Alaska Native |  |  |  |
| Asian |  |  |  |
| Native Hawaiian or Other Pacific Islander |  |  |  |
| Black or African American |  |  |  |
| White |  |  |  |
| **Racial Categories: Total of All Subjects*** |  |  |  |

**The “Ethnic Category: Total of All Subjects” must be equal to the”Racial Categories: Total of All Subjects”.*

*- Identify the criteria for inclusion or exclusion of any subpopulation.*

*- Explain the rationale for the involvement of special classes of subjects, such as fetuses, neonates, pregnant women, children, prisoners, institutionalized individuals, or others who may be considered vulnerable populations. Note that 'prisoners' includes all subjects involuntarily incarcerated (for example, in detention centers) as well as subjects who become incarcerated after the study begins.*

*- If you propose to exclude any sex/gender or racial/ethnic group, include a compelling rationale for the proposed exclusion. For example, 1) the research question addressed is relevant to only one gender or 2) evidence from prior research strongly demonstrates no difference between genders.*

*- Provide either a description of the plans to include children or, if children will be excluded from the proposed research, then you must present an acceptable justification for the exclusion. For example, 1) the condition is rare in children as compared to adults or 2) insufficient data are available in adults to judge risk in children.*

*- List any collaborating sites where human subjects research will be performed, and describe the role of those sites in performing the proposed research.*

Thad E. Saleeby Center in Hartsville, South Carolina

b. Sources of Materials

*- Describe the research material obtained from living human subjects in the form of specimens, records, or data.*

*- Describe any data that will be recorded on the human subjects involved in the project.*

*- Describe the linkages to subjects, and indicate who will have access to subject identities.*

*- Provide information about how the specimens, records, or data are collected and whether material or data will be collected specifically for your proposed research project.*

The researchers working on this study will analyze the clinical information that is already routinely collected on the individuals at the Saleeby Center. This information includes observed seizures, sleep patterns and behavior. The researchers may also collect other information including the individuals medications as well as pretinent baseline information collected during the time prior to the study (e.g., seizure frequency, sleep patterns, behavior).

All of the data will be associated with a non-identifying number in place of the subject's name. Physical data will be locked up and electronic data will be password-protected. Only members of the research team will have access to this information.

c. Potential Risks

*- Describe the potential risks to subjects (physical, psychological, social, legal, or other), and assess their likelihood and seriousness to the subjects.*

*- Where appropriate, describe alternative treatments and procedures, including the risks and benefits of the alternative treatments and procedures to participants in the proposed research.*

There are minimal risks involved with this study. There is a slight chance that the music might disrupt a subject's sleep patterns. To prevent this from happening, the volume level of the Mozart music will be adjusted so that it does not wake them up or prevent them from falling asleep. Preliminary research at the Medical University of South Carolina by the principle investigator has shown that the music exposure does not affect a subject's sleep cycle.

2. ADEQUACY OF PROTECTION AGAINST RISKS

a. Recruitment and Informed Consent

*- Describe plans for the recruitment of subjects (where appropriate) and the process for obtaining informed consent. If the proposed studies will include children, describe the process for meeting requirements for parental permission and child assent.*

*- Include a description of the circumstances under which consent will be sought and obtained, who will seek it, the nature of the information to be provided to prospective subjects, and the method of documenting consent.*

Participants will be recruited from the current residents of the Thad E. Saleeby Center. Informed consent will obtained by the principle investigator, [name]. Since the majority of the individuals are unable to give informed consent, special language has been included in the consent form for the parent/legal guardian acting on the individual’s behalf in accordance with the South Carolina Department of Disabilities and Special Needs (Form 535-07-PD).

b. Protection against Risk

- *Describe planned procedures for protecting against or minimizing potential risks, including risks to confidentiality, and assess their likely effectiveness.*

*- Where appropriate, discuss plans for ensuring necessary medical or professional intervention in the event of adverse effects to the subjects.*

*- Studies that involve clinical trials (biomedical and behavioral intervention studies) must include a description of the plan for data and safety monitoring of the research and adverse event reporting to ensure the safety of subjects in Section 4 below.*

The only change from normal care that is being proposed is that Mozart music will be quietly played in the background in one group of individuals. The data collection that will yeild the primary and secondary outcome measures is the same protocol that is already in place at the Saleeby Center. One possible risk is that an individual's sleep patterns may be distrubed. Preliminary studies at the Medical University of South Carolina by the principle investigator have shown that sleep cycles are not altered by the music. Special care will be taken to tailor the volume threshold on a patient-to-patient basis.

The risk of compromising protected health information (PHI) will be minimized by locking up physical medical records and password-protecting computer records. Only staff at the Thad E. Saleeby Center and members of the research team will have access to the research files.

3. POTENTIAL BENEFITS OF THE PROPOSED RESEARCH TO THE SUBJECTS AND OTHERS

*- Discuss the potential benefits of the research to the subjects and others.*

*- Discuss why the risks to subjects are reasonable in relation to the anticipated benefits to subjects and others.*

The potential benefit is that the music may decrease the frequency of an individual's seizures. The subjects' sleep patterns and behavior may also benefit from the exposure to Mozart. If this is the case, it is possible that this treatment could be used as a supplemental therapy for epilepsy. It is hoped that the information gained from this study will help researchers in the understanding and treatment of children and adults with epilepsy.

4. IMPORTANCE OF THE KNOWLEDGE TO BE GAINED

*- Discuss the importance of the knowledge gained or to be gained as a result of the proposed research.*

*- Discuss why the risks to subjects are reasonable in relation to the importance of the knowledge that reasonably may be expected to result.*

*- NOTE: Test articles (investigational new drugs, devices, or biologicals) including test articles that will be used for purposes or administered by routes that have not been approved for general use by the Food and Drug Administration (FDA) must be named. State whether the 30-day interval between submission of applicant certification to the FDA and its response has elapsed or has been waived and/or whether use of the test article has been withheld or restricted by the Food and Drug Administration, and/or the status of requests for an IND or IDE covering the proposed use of the test article in the research plan.*

The risk/benefit assessment for this project is excellent. The subjects are exposed to no more than minimal risk and the results, if valid, represent a significant non-invasive treatment for reducing seizure frequency, improving sleep patterns and reducing behavioral problems. Joining the research project is completely optional and if a subject joins and later decides to leave the study, they may do so without fear of penalty or loss of benefits.

5. SUBJECT SAFETY AND MINIMIZING RISKS (Data and Safety Monitoring Plan)

*Studies that involve *clinical trials (see description below) must include a description of the plan for subject safety and minimizing risks of the research, including data monitoring and adverse event reporting to ensure the safety of subjects. The complexity of the plan should be determined by the level of risk to subjects. The plan should specify: 1) what will be monitored, 2) how frequently the monitoring will occur, 3) who will be responsible for the monitoring, and 4) study endpoints.*

Data and safety monitoring will be the responsibility of the principle investigator ([name]) and the Co-directors of the Thad E. Saleeby Center ([name] and [name]).

1) The primary outcome that will be monitored will be seizure frequency. The staff at the Saleeby Center are trained to observe seizure activity and maintain a detail record of such events. The secondary outcome measures include sleep patterns and changes in behavior. At night, the staff is required to check on each patient every 30 minutes and record if they are asleep or not. Certain behavioral characteristics (screaming, hitting, nail-biting, crying, inappropriate undressing, etc.) are recorded for each individual.

2) The individuals are monitored around the clock. Data will be collected for one calendar year. Since the outcome measures that will be collected for the study are the same pieces of information that have already been recorded for their clinical management, a detailed baseline comparison can be made with previous years.

3) Data monitoring will be the responsibility of the staff at the Thad E. Saleeby Center. Seizures, sleep patterns and behavioral changes will be recorded as usual by the nurses. Specific behavioral measures will be monitored by the clinical psychologist, [name].

4) The study will end exactly one calendar year after it begins. The tentative start date is January 1, 2006.

*Clinical Trials

*A* clinical trial *is a prospective biomedical or behavioral research study of human subjects that is designed to answer specific questions about biomedical or behavioral interventions (drugs, treatments, devices, or new ways of using known drugs, treatments, or devices).*

*Clinical trials are used to determine whether new biomedical or behavioral interventions are safe, efficacious, and effective. Behavioral human subjects research involving an intervention to modify behavior (diet, physical activity, cognitive therapy, etc.) fits these criteria of a clinical trial. Human subjects research to develop or evaluate clinical laboratory tests (e.g. imaging or molecular diagnostic tests) might be considered to be a clinical trial if the test will be used for medical decision-making for the subject or the test itself imposes more than minimal risk for subjects.*

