**D. RESEARCH DESIGN AND METHODS (including data analysis) __________________________________**

*Describe the research design and the procedures to be used to accomplish the specific aims of the project. Include how the data will be collected, analyzed, and interpreted and specify what statistical methods will be used. Describe any new methodology and its advantage over existing methodologies. Discuss the potential difficulties and limitations of the proposed procedures and alternative approaches to achieve the aims. As part of this section, provide a tentative sequence or time-table for the project. Point out any procedures, situations, or materials that may be hazardous to personnel and the precautions to be exercised.*

Study Subjects: Individuals at the Thad E. Saleeby Center are all candidates for participation in this study. The ages will range from 5 to 90 years old.

Inclusion criteria:

• Resident of the Thad E. Saleeby Center

• Epilepsy or seizure disorder

• At least one year of detailed seizure reporting prior to study starting date

Exclusion criteria:

• Severe hearing impairment

Written informed consent will be obtained for all participants. If an individual is not capable of giving informed consent, a parent or legal guardian will be asked to act in the best interest of the patient in accordance with DDSN Departmental Directive 535-07-PD (see consent form for more details).

Children and adults who have given informed consent to participate in this study will be randomized into two groups: Group 1 (2/3 of participants) will be exposed to Mozart music at night and Group 2 (1/3 of participants) will be exposed to silence at night. Special care will be taken to make sure the audio levels for Group 1 do not disrupt their sleep cycles. Preliminary data from a pilot study at MUSC shows that background music does not alter sleep patterns.

Group 1 Protocol: Exposure to K448 will occur nightly between the hours of 9:00 p.m. and 7:00 a.m. Each room will have a sound system installed in it to deliver the stimuli. The stimuli will be presented in the same pattern as the 2002 ten-subject pilot study at MUSC:

Pre-exposure: The first 9 minutes of each hour will be silent.

Exposure: 8.5 minutes of K448 will follow the silent baseline.

Post-exposure: 8.5 minutes of silence will follow K448 acting as a washout.

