The exposure and post-exposure epochs will play 3 times each hour before the cycle repeats the following hour beginning with another 9 minute baseline. Since the cycle is exactly 60 minutes in length, we will be able to deliver the entire stimulus train on one 80-minute compact disk from a central location in the Saleeby Center.

Group 2 Protocol: No music will be played for the control group. Evening and morning routines for both groups should remain identical.

Data Collection: A tentative start date for the project is January 1, 2006. Prior to this date, it is important to outline what data will be collected. The primary outcome measure for the study is seizure frequency. Therefore detailed records of seizure frequency by the Saleeby staff will be critical to quantifying any significant changes compared to baseline (previous years). Duration and intensity of seizures would also be useful as secondary measures of outcome in addition to sleep patterns and behavior.

Data will be collected on each individual for each outcome measure during the 12 month period of exposure. Interim analyses will occur monthly, quarterly, and at 6 months into the study.

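### Nurses who can very probably tell the arm at night record the primary outcome, and the protocol contradicts itself on whether Center staff may see the research files

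*Protocol*

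**What the plan says.** All references are to the protocol.

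- **Outcome and recorder.** Section E.5, item 1: "The primary outcome that will be monitored will be seizure frequency". It is obtained by observation: "The staff at the Saleeby Center are trained to observe seizure activity and maintain a detail record of such events". Item 3: "Seizures, sleep patterns and behavioral changes will be recorded as usual by the nurses".
- **Arms.** Section D, Group 1 Protocol: "Each room will have a sound system installed in it to deliver the stimuli". Music is scheduled between 9 p.m. and 7 a.m. Group 2 Protocol: "No music will be played for the control group".
- **Night contact.** Section E.5, item 1: "At night, the staff is required to check on each patient every 30 minutes and record if they are asleep or not".
- **Access.** Section E.1.b, on the coded study data: "Only members of the research team will have access to this information". In Section E.2.b the closing sentence on confidentiality begins by naming the staff of the facility and continues: "Center and members of the research team will have access to the research files".
- **Interim looks.** Section D, Data Collection, plans analyses monthly, quarterly and at six months, and does not say who sees them.
- **Masking.** None is described for this trial. Blinding is mentioned only in Section C, for an earlier pilot that used control music.

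**The concern.** Whether an event is noticed, judged to be a seizure and written down depends on the observer. Here the observer can very probably tell the arm for part of each day, and the comparator does nothing to conceal it. If knowing the arm changes vigilance or the threshold for writing an event down, the recorded rates differ between arms even when the true rates do not.

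The two access statements add a second, avoidable route. Under E.2.b, Center staff may open the research files; under E.1.b they may not, unless they count as research team. Until this is settled, the protocol gives no assurance that recorders cannot see the allocation or the results of frequent interim looks.

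The credibility of the primary comparison is at stake. Longer follow-up does not help: it narrows the interval around the biased value. Later analysis cannot recover events that were never recorded.

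**Working it through.** The protocol states no sample size, effect size or SD, so there is no design figure to reproduce.

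**1. Would night staff meet the music?** Section D gives 9 minutes of silence, then three rounds of 8.5 minutes of music and 8.5 of silence.

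- Cycle: 9 + 3 × (8.5 + 8.5) = 60 minutes, as the protocol says.
- Music: 3 × 8.5 = 25.5 minutes per hour (42.5%), at minutes 9–17.5, 26–34.5 and 43–51.5.
- Two checks 30 minutes apart, the first at minute t (0 to 30): at least one meets music when t lies in 0–4.5, 9–21.5 or 26–30. That is 4.5 + 12.5 + 4 = 21 of 30 minutes, or 70% of start times.
- Checks on the hour and half-hour always meet music at the half-hour.

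Over ten hours a night for a year, it is very unlikely that night staff would not know.

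**2. Does the baseline protect?** Let θ be the true rate ratio and d the share of seizures recorded. The baseline-adjusted ratio that is observed is

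θ × (d music, after ÷ d music, before) ÷ (d silence, after ÷ d silence, before).

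Baseline removes only differences in recording that stay constant. The earlier records predate allocation, so a shift in one arm after the start remains in the result.

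**3. How large would it have to be?** Assumptions, not from the protocol: no true effect, comparison of log rate change, two-sided alpha 0.05, SD 0.3, 0.5 or 0.8. N = 85 and 92 take every current resident (Section H) as enrolled, which is an upper limit; N = 45 is a smaller illustration. With the 2:1 allocation of Section D,

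SE = SD × √(3/N + 1.5/N) = SD × √(4.5/N), and the loss q that alone gives p = 0.05 is 1 − exp(−1.96 × SE).

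Example: N = 85, SD 0.5: SE = 0.5 × √(4.5/85) = 0.115; q = 1 − exp(−0.2255) = 20.2%.

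| SD | q for p = 0.05 at N = 45 / 85 / 92 | Chance of a significant result for music if q = 20%, same N |
|---|---|---|
| 0.3 | 17.0% / 12.7% / 12.2% | 65% / 90% / 92% |
| 0.5 | 26.6% / 20.2% / 19.5% | 29% / 49% / 52% |
| 0.8 | 39.1% / 30.3% / 29.3% | 14% / 23% / 24% |

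Here q is the relative loss in the whole 24-hour count.

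**4. What does that mean for the night?** Music hours are 10 of 24. If seizures are spread evenly and only night recording is affected, q = (10/24) × night loss, so night loss = 2.4 × q.

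- A 10%–20% loss overall needs 24%–48% at night.
- The p = 0.05 thresholds at N = 85–92 become about 29%–30%, 47%–48% and 70%–73% for the three SDs.

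If all seizures fell at night, the night loss would equal q. The true share is not given.

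**The case against.** The strongest reply is that recording follows the Center's existing routine, the staff are trained, full masking of audible music against silence is hard to achieve, and the access sentence in E.2.b concerns confidentiality. Much of this is fair. Center staff create the clinical records, so some access is unavoidable. Splitting counts by time of day is also commonly settled in a statistical analysis plan, so its absence here is no fault. The unchanged forms do not answer the point, however: what changes is what the observer knows. Who records and who has access are matters the protocol itself fixes.

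A reader might infer more than the protocol supports:

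- **That file access unmasks the day staff.** Neither access section says the files hold the allocation. The supportable statement is that recorders are not protected from learning it.
- **That there is a separate, unaware day team.** No section describes shifts, rotation or handover.
- **That music drowns out seizures.** No section says staff detect seizures by sound, and the music is described as quiet background.
- **That a rate ratio of 0.80–0.90 is the expected bias.** This merely restates an assumed 10%–20% under-recording.
- **That the bias must favour K448.** Volume is to be set individually (Section E.2.b), and extra attention to music rooms could equally raise detection there.

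**Conclusion.** The point holds as a risk to the primary comparison, not as a demonstrated bias. The outcome is observer-dependent, night recorders can very probably tell the arm, no masked or objective check is described, and the access statements conflict. That night staff hear the music is inferred from the room speakers, half-hourly checks and silent control; the protocol does not say it.

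Size and direction are unknown. The figures show only what would suffice under the assumed SD, alpha and N. With nearly all residents enrolled and modest between-patient variation, a moderate loss in the whole count could produce a significant result by itself. With recording affected only at night and seizures spread evenly, the night loss would have to be large. The access conflict is secondary: the music alone very probably reveals the group at night.

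**What to change.** 1. **Reconcile Sections E.1.b and E.2.b.** Staff who record outcomes keep access to their own clinical records, but not to the allocation list or to the monthly, quarterly and six-month interim results. Where practicable, daytime recorders are not told the allocation.
2. **Report seizure counts separately** for 9 p.m.–7 a.m. and 7 a.m.–9 p.m., in the protocol or the statistical analysis plan. Treat the day count as a supportive sensitivity analysis, not as a gate on the conclusion. A rule that it must merely point the same way would pass about half the time by chance with no day effect, and could block a real effect confined to the night.
3. **State unmasked ascertainment** as a limit on the claim.

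The cost is wording, access control and one further analysis of existing logs, provided they hold the time of day. The day count is less precise, misses a night-only effect, and is only partly protected if the same nurses work both shifts or share information. A masked or objective check on a sample of events would address the problem more directly, but would need new procedures.
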